#### 1- and 2-Year Follow-Up

Visits will occur at 1, 2, and 3 years post partum (SD 1 month). The questionnaire includes child health and vitamin, mineral or other medicine intake; breastfeeding and infant feeding; maternal diet; alcohol consumption; Postpartum Specific Anxiety Scale [13]; Edinburgh Postnatal Depression Scale [15]; and the brief infant sleep questionnaire–short form [16]. At 1 year post partum, child development will be assessed using caregiver-reported early development instruments [14]. At 2 and 3 years post partum, child development will be assessed using the Global Scale for Early Development [17]. Hemoglobin levels of the mother and infant will be taken using the HemoCue Hb 301. Biospecimen samples include infant feces and human milk. Anthropometric measurements of the child included foot length, skinfold thickness of the triceps, subscapular, quadriceps, and flank, weight, length, MUAC, and head circumference. Anthropometric measurements of the mother included skinfold thickness of the triceps, subscapular, quadriceps, and flank, blood pressure, height, weight, and heart rate.

### Retention of Participants

In order to reduce participant dropout, we collect a variety of contact information. Participants provide their first and family name, address, phone number, email address, village leader name, temple or religious organization, and the contact information of a family member or close friend. In addition, we provide a small incentive. Immediately after the physical examination, all participants receive the test results for both the mother and child and can track their progress over time at each visit. Test results include blood pressure, hemoglobin levels, and all anthropometric values. Results are explained in person and written on an information pamphlet. All participants who complete the baseline questionnaire receive a small gift that equates to approximately US $1.

### Outcomes

The primary end point will be exclusive breastfeeding at 6 months postpartum. Secondary end points will include exclusive and complementary breastfeeding duration, childhood wasting and stunting, child growth (height and weight), maternal and infant stress, predictors of early breastfeeding cessation, intestinal inflammation, anemia, maternal weight loss, maternal blood pressure, maternal anxiety, and GRIT personality score.

### Data Management

The ODK is used for all questionnaires and data management. All study staff have access to an Android tablet with the ODK Collect app. Data collection is completed offline on password-protected devices. Data connectivity is only used to send the final questionnaire data.

Project data will only be accessible to authorized personnel who require the data to fulfill their duties within the scope of the research project. On the case report forms and other project-specific documents, participants are only identified by a unique participant number. The unique participant number will be taken directly from VITERBI, and is a combination of the household number, district, village, and individual within the household. Health-related data will be stored for 15 years, following institutional storage and safety policies. Only samples will be kept for an unidentified amount of time if the separate consent for reuse of health data has been signed. Data storage is on a locally secured server using the ODK Aggregate server and secured via a secure sockets layer.

Biological material in this project is not identified by participant name but by a unique participant number. Biological material is appropriately stored in a restricted area only accessible to authorized personnel. The biological specimens will be stored with their code at Lao TPHI and Swiss TPH.

### Ethical Considerations

Ethical approval for the study was obtained from the Ethics Commission of Northwestern and Central Switzerland (EKNZ, 2020-00037) and from the National Ethic Committee for Health Research (044/NECHR; June 30, 2021). This research project will be conducted in accordance with the protocol, the Declaration of Helsinki [3], the Swiss Human Research Act, and the Swiss Human Research Ordinance [1], as well as other locally relevant regulations. Patients or the public were not involved in the design, conduct, reporting, or dissemination plans of our research. Eligible participants will be visited initially by study staff. The purpose of the study and its procedures will be explained to participants and written informed consent will be obtained. Pregnant women will be giving consent for themselves and their newborns. For minors (aged <18 years), both the pregnant woman and her parents will provide consent. For participants who are illiterate, there will be an additional witness who is not part of the study team. Participation is voluntary and patients have the right to withdraw from the study at any given point in time with no further obligations. If the participant withdraws at any time, all data will be deleted and biospecimen samples destroyed. Confidentiality of information will be assured to the participants. All participants younger than 18 years are considered vulnerable populations according to the Lao PDR legislation. If the respondent is underage and agrees to participate, he or she needs the authorization of a parent or legal guardian, who cosigns the study informed consent.

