### Sample Size Calculation and Power

Enrolling 100 participants for each intervention arm provided us with 80% power to detect an increase in exclusive breastfeeding from the anticipated 21% in the control arm to 40% in either of the 2 intervention arms.

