### Study Logistics

During the baseline visit, if informed consent was given, a random number was generated within the Open Data Kit (ODK) platform that assigned the mother to a control or intervention group. If they were randomly assigned to an intervention group, mothers were allowed to choose from the following social transfers: (1) money (US $75); (2) developmental toys, clothes, and diapers for the child; or (3), a combination of money and developmental toys, clothes, and diapers for the child (Figure 1). We created a shopping catalog with different toys and clothes for them to choose from. At the end of the visit, the study team encouraged intervention group 1 to meet their breastfeeding goals and told them that the social transfer would be provided at 6 months post partum to show our support for their breastfeeding efforts. Mothers randomly selected for the third intervention arm were told that they would only receive their social transfer if they exclusively breastfed and nurses could observe breastmilk expression at the 6-month visit. All intervention and control groups received educational material about the benefits and recommendations of exclusive breastfeeding.

During a follow-up visit when the child is 6 months of age, nurses will collect an end-line survey from mothers, collect infant fecal samples, and observe breastmilk expression.

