## Results

As of November 2023, the study has enrolled 300 participants. Study participation is ongoing until December 2027 at minimum. Over the study lifetime, 93% have completed all visits. Primary results from the 6-month visit are expected in early 2024.

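### Deleting all data at any withdrawal drops randomised mothers, can erase 6-month outcomes already observed, and makes the primary result non-reproducible; the size of any bias is unknown

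*Protocol article*

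**What the plan says.** The article's Ethical Considerations section gives mothers an open-ended right to leave: "patients have the right to withdraw from the study at any given point in time with no further obligations". It attaches this consequence: "If the participant withdraws at any time, all data will be deleted and biospecimen samples destroyed".

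Four other places fix the timing:

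- **Allocation** takes place at the baseline visit, about 1 month post partum, after consent (Study Logistics): "a random number was generated within the Open Data Kit (ODK) platform that assigned the mother to a control or intervention group".
- **Primary endpoint** (Outcomes): "The primary end point will be exclusive breastfeeding at 6 months postpartum".
- **Reporting** (Results): "Primary results from the 6-month visit are expected in early 2024".
- **Follow-up** lasts at least 3 years post partum (Discussion). The Results section adds "Study participation is ongoing until December 2027 at minimum", whereas the Abstract and the Methods Overview give December 2026.

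Data Management sets a 15-year storage period but exempts nothing from the deletion rule: not the allocation, not the primary outcome, not a locked dataset.

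**The concern.** Withdrawal happens after randomisation, so deleting everyone who withdraws makes the analysis set depend on a post-randomisation event. Ordinary loss to follow-up leaves a known arm and a missing outcome, which can be counted or bounded. Deletion as written leaves no individual record of either.

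Three things are at stake:

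- The denominator shrinks below the number randomised.
- A 6-month outcome already recorded can be removed before it is analysed.
- Once the primary result has been obtained, a later withdrawal leaves a dataset from which it cannot be reproduced.

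The rule also discards follow-up time up to withdrawal, which the secondary endpoints on breastfeeding duration could otherwise use.

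A link between withdrawal and arm is conceivable. Mothers in the conditional arm were told that "they would only receive their social transfer if they exclusively breastfed and nurses could observe breastmilk expression at the 6-month visit", so a mother in that arm who has stopped exclusive breastfeeding has no transfer left to gain. This is a possible mechanism; the article reports no imbalance.

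**Working it through.** **Inputs.** 100 mothers per arm, 21% in control and 40% in an intervention arm (Sample Size Calculation and Power); 300 enrolled and 93% completing all visits (Results); enrolment August 2022 to April 2023 (Abstract). Not stated, so assumed: alpha 0.05 two-sided. The number of withdrawals is not given; 3 to 15 per 100 is used as a range.

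**1. The plan's own figure.** The article states: "Enrolling 100 participants for each intervention arm provided us with 80% power". The usual two-proportion formula is n = [1.960·√(2·p̄·q̄) + 0.842·√(p₁q₁ + p₂q₂)]² / d², with p̄ = 0.305 and d = 0.19. This gives (1.276 + 0.536)² / 0.0361 = 91 per arm, and 83.6% power at 100 per arm. With continuity correction it gives 102 per arm, and about 79% power at 100. The stated 80% is reproduced.

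**2. Loss of precision.** Uncorrected power is 80.9% at 93 per arm, 79.6% at 90 and 77.2% at 85. Precision is not the main issue.

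**3. Worst case in one arm.** Delete w mothers from an arm of 100, all non-exclusive. The observed rate becomes 100p/(100 − w):

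| w | true 40% reads | true 21% reads |
|---|---|---|
| 3 | 41.2% | 21.6% |
| 7 | 40/93 = 43.0% | 21/93 = 22.6% |
| 10 | 40/90 = 44.4% | 21/90 = 23.3% |
| 15 | 47.1% | 24.7% |

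**4. Less extreme cases.**
- The same 7 deletions in both compared arms: 40/93 − 21/93 = 19/93 = 20.4 points, an excess of 1.4 over the planned 19.
- Only non-exclusive mothers in one arm leave, at 7%: 60 × 0.93 = 55.8 remain, and 40/(40 + 55.8) = 41.8%, an excess of 1.8.
- Withdrawal unrelated to outcome: expected bias zero.

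**5. What the rule itself adds.** A mother who withdraws before 6 months has no 6-month outcome, whether or not her earlier data are kept. Take 7 non-exclusive withdrawals in an arm with a true 40%, and compare observed-case rates with and without deletion:
- All 7 leave before the visit: 40/93 = 43.0% either way, so the rule adds 0.
- 4 before and 3 after: 40/96 = 41.7% if data are kept, 43.0% if deleted. The rule adds 1.3 points.
- All 7 after: 40.0% if kept, 43.0% if deleted. The rule adds 3.0 points.

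**6. Exposure window.** Enrolment at about 1 month places the 6-month visits about 5 months later, roughly January to September 2023. With results due in early 2024, an observed outcome is exposed to deletion before analysis for about a year for the first mothers and a few months for the last. Later withdrawals, to the end of 2026 or 2027, affect reproduction of the result, not the result already obtained.

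**7. What a count per arm would rescue.** If 93 records remain, 40 of them exclusive, and the tally shows 7 deleted, the arm's rate lies between 40/100 = 40% and 47/100 = 47%. Without the tally, neither bound can be formed.

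**The case against.** The best defence is that the rule protects participants, in a study approved by two ethics committees, and that its effect on the primary result may be nil. Most of this defence stands.

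- The incentive to leave acts mainly before the 6-month visit, when the transfer is decided, and those outcomes would be missing anyway.
- Control mothers have no transfer to gain either, so the incentive argument does not show that conditional-arm mothers who have stopped leave more often than controls.
- A reader might take the 7% who did not complete all visits as the withdrawal rate. The article does not support that. Missed visits do not trigger deletion, and the Discussion gives another possible reason for them: impassable roads in the rainy season.
- A reader might also infer that an intention-to-treat result becomes impossible, or that loss by arm can never be computed. That goes too far. The rule concerns a participant's data, not aggregate counts, and a tally per arm is enough for bounds. The article does not name an intention-to-treat population.
- Terms on anonymisation may stand in the full protocol or consent form, which are not shown.

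The defence does not remove the core point. The rule is stated for any time and all data. Followed as written, it deletes outcomes of mothers who leave after the 6-month visit, and the article provides for no retained count or fixed dataset. An analysis plan can limit the damage only if the counts are kept when deletions occur.

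**Conclusion.** The concern holds in limited form: a cheap improvement of moderate severity. The deletion rule removes randomised mothers, can erase observed 6-month outcomes in the months before the primary analysis, and makes the primary result non-reproducible after any later withdrawal.

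The size of any bias cannot be established from the article and may be zero. A shift of 3.0 points (40% to 43.0%) needs 7 deletions per 100 in one arm, all non-exclusive. For the rule itself to cause the whole shift, all 7 must also leave after the 6-month visit and before the analysis. A reader might infer that the rule inflates the effect by 3 to 4 points; no withdrawal count, split by arm or timing in the article supports that. The loss of reproducibility needs no assumption about bias: one later withdrawal is enough.

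**What to change.** **Now, within the existing consent and approvals:**
1. Keep a de-identified tally, by arm, of mothers randomised, withdrawn and deleted, split into before and after the 6-month visit.
2. Use all randomised mothers as the denominator of the primary analysis, with best- and worst-case bounds for those deleted. Report withdrawals separately from missed visits.
3. Fix the 6-month analysis dataset in anonymised form before the primary analysis, as far as the consent given and the ethics approvals allow.

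**By amendment, subject to both ethics committees and re-consent:** withdrawal stops new data collection, while data already collected are kept in coded or anonymised form.

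**Cost.** The tally and bounds cost little. The amendment comes late, because all 300 mothers are already enrolled: it means two ethics submissions and re-consent across the cohort, and less than full erasure for mothers who agree. Mothers who do not agree stay under the present rule, so the tally and bounds are needed in any case.

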## Results

As of November 2023, the study has enrolled 300 participants. Study participation is ongoing until December 2027 at minimum. Over the study lifetime, 93% have completed all visits. Primary results from the 6-month visit are expected in early 2024.

## Discussion

Conditional cash transfer programs have been used in a wide range of settings to reduce poverty, with proven benefits for short- and long-term health [18]. STEB is to our knowledge the first longitudinal and randomized social transfer program evaluation for breastfeeding in a low- or middle-income country. We will follow participants for a minimum of 3 years post partum—providing an excellent platform to investigate the short- and long-term benefits of a breastfeeding social transfer program.

During the first year of the program, we encountered a variety of barriers. To start, enrolling new mothers at approximately 1 month post partum was difficult due to the high rates of infant formula use. We strategically enrolled at 1 month post partum to reduce coercion among mothers who did not want to breastfeed. However, a large majority of mothers provided infant formula before 1 month post partum. Enrolling mothers earlier in the postpartum period who want to exclusively breastfeed may reduce the early introduction of infant formula. Second, distances between the 4 study districts in Vientiane, Lao PDR are large. Transportation of staff to the rural districts is a major challenge because of the time spent traveling and the high burden of transportation costs. For example, during the rainy season, many streets become impassable—reducing the capabilities of the study staff to reach participants. Collection of infant fecal samples at 1-month was also difficult because of the irregularity of bowel movements at this age.

Despite the substantial size of the social transfers made, we believe that interventions that include financial support for breastfeeding can be highly cost-effective in this setting. In 7 Southeast Asian countries alone, the short- and long-term benefits of breastfeeding are estimated at US $1.9 billion a year [1]. We believe that social transfer programs focused on breastfeeding have the potential to be more effective in low- or middle-income countries, where monetary compensation may reduce additional barriers not present in high-income countries.

STEB has some limitations worth noting. The small sample size will prohibit more nuanced data analysis. Enrollment does not occur immediately after birth; instead, all participants are enrolled at 1-month post partum. Many mothers face significant barriers to exclusive breastfeeding during the first month postpartum; therefore, the study population of STEB may be slightly different. Recall of the exact timing of complementary foods provided is likely biased; yet, previous research has shown that recall bias for breastfeeding is minimal.

STEB was designed to provide a unique platform to investigate the short- and long-term impacts of exclusive and complementary breastfeeding on child health and development. Further, the longitudinal sampling of human milk and infant feces provides a unique opportunity to study human milk as a biological system and how this impacts the gut microbiome. If proven effective, we see potential for a long-term program that may be implemented in other low- or lower-middle-income countries with only minor modifications.

## Appendix

Multimedia Appendix 1 Peer-review report by the Swiss National Science Foundation.

## Abbreviations

Lao PDR: Lao People’s Democratic Republic
MUAC: mid-upper arm circumference
ODK: Open Data Kit
RCT: randomized controlled trial
STEB: Social Transfers for Exclusive Breastfeeding
VITERBI: Vientiane Multigenerational Birth Cohort
